# HANDLING OF UNEXPECTED OR ADVERSE EVENTS

**Response to new or unexpected findings**

All treatment failures will be treated with quinine as per the National Guidelines. If sufficient number of malaria cases are presenting to the clinic but enrolment is insufficient, the supervisor will need to determine at what point the problem with enrollment is occurring, and take steps needed to rectify the problem. If the problem is not remedied, the supervisor will report the poor enrollment to the investigators at CDC, Atlanta, and steps will be taken to either rectify the problem or to find a new site.

**Identifying, managing and reporting adverse events**

The combination of artemether + lumefantrine has been shown to be safe and highly efficacious [25]. Studies of all of these combinations have reported only mild or moderate adverse events, including dizziness, headache, anorexia, nausea and abdominal pain, noting that these events may also be attributable to malaria.

Severe allergic reactions have not been reported in association with artemisinin use. Anaphylactic type reactions to artemisinins have been reported very infrequently; these are estimated to occur in 1 in 2833 patients who receive an artemisinin (95% confidence interval 1 in 1362 to 6944; 6/ 17,000 patients)[27]. There has been one additional report of angioedema suspected to be due to the artemether component of artemether-lumefantrine[28]. With the initial development of AL, its safety was compared to CQ in the treatment of falciparum malaria. An efficacy study in Tanzanian children reported no serious adverse events in either group [29]. Two other studies comparing AL with CQ for the treatment of falciparum malaria noted more frequent reports of pruritus and vomiting in the CQ group [30, 31]. We will be observing all the children for an hour following the ingestion of every dose of antimalarial. Most severe allergic reactions will manifest within an hour of taking the dose. We will council patients and parents to return immediately if they or their child develops a raised rash (urticaria) or difficulty breathing suggestive of a severe allergic reaction.

In the event of mild adverse reactions, it will be noted in the subjects case report form that these occurred; no further action will be taken by staff members, except in the case of vomiting, in which case the treatment medication may need to be re-administered.

In the event of significant vomiting, initially ORS (oral rehydration solution) will be administered, if this is not tolerated the patient will be referred to the district hospital for further management. In the case of any severe adverse reaction (difficulty breathing, convulsions, and change in mental status) subjects will be referred to the district hospital for management. Transportation to the hospital will be provided.

Any adverse event which is severe, unexpected, and possibly related to the study, as well as any unanticipated problems involving risks to subjects or others and any occurrences of serious or continuing non-compliance will be reported to the CDC IRB according to CDC policy on incident reporting.

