**Classification of Treatment Outcomes, WHO 2003**

**Early Treatment Failure (ETF)**

- Development of danger signs or severe malaria on day 1, day 2 or day 3 in the presence of parasitemia
- Parasitemia on day 2 higher than day 0 count irrespective of axillary temperature
- Parasitemia on day 3 with axillary temperature ≥37.5 ºC
- Parasitemia on day 3 ≥25% of count on day 0

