**Late Treatment Failure (LTF)**

***Late Clinical Failure* (LCF)**

- Development of danger signs or severe malaria after day 3 in the presence of parasitemia, without previously meeting any of the criteria of Early Treatment Failure
- Presence of parasitemia and axillary temperature ≥37.5 ºC or history of fever on any day from day 4 to day 28 or 42, without previously meeting any of the criteria of Early Treatment Failure

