**Adequate Clinical and Parasitological Response (ACPR)**

- Absence of parasitemia on day 28 or 42 irrespective of axillary temperature without previously meeting any of the criteria of Early Treatment Failure or Late Clinical Failure or Late Parasitological Failure

In order to differentiate a recrudescence (same parasite strain) from a newly acquired infection (different parasite strain), a genotypic analysis based on merozoite surface protein-1 (*msp1)*, merozoite surface protein 2 (*msp2)* and glutamate-rich protein (*glurp)* will be performed by PCR for Pf. Additionally, we will characterize microsatellite markers for Pf to differentiate recrudescence from reinfection and potentially assess for drug resistance markers.

**Definition of Treatment Outcomes for *P. vivax* infections, WHO 2002** [4]

Treatment failure defined as:

1. Clinical deterioration due to *P. vivax* illness requiring hospitalization in presence of parasitemia
2. Presence of parasitemia and axillary temperature ≥37.5oC any time between Day 3 and Day 28 or 42
3. Presence of parasitemia on any day between day 7 and day 28 or 42, irrespective of clinical conditions.

*P. vivax* infections that recur after drug treatment can have 1 of 3 etiologies: 1) recrudescence, 2) reinfection, or 3) relapse arising from the dormant liver stage (hypnozoites). In order to differentiate the treatment failures as recrudescence or relapse from a newly acquired infection, a genotypic analysis based on P. vivax circumsporozoite protein (*pvcs*), the merozoite surface protein 1 (*pvmsp1*) and the merozoite surface protein 3-alpha (*pvmsp3-alpha*) will be performed by PCR for Pv. Additionally, we also will characterize microsatellite markers to assess recrudescence from reinfection and for drug resistance markers. Those who fail in the vivax arms will have drug levels tested from the already collected filter paper.

**Valid end-points** include treatment failure, completion of the follow-up period without treatment failure, loss to follow-up, withdrawal from study (voluntary or involuntary, and protocol violation). Loss to follow-up occurs when, despite all reasonable effort, an enrolled patient who does not attend the scheduled visits, cannot be found. Patients who withdraw from the study during the treatment period (days 0-2) will be treated with AL or CQ depending on the species according to the national policy. They will be referred back to the clinic to continue with care.

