**Criteria for withdrawal**

Patients meeting any of the following criteria will be withdrawn:

- Withdrawal of consent
- Failure to complete the treatment
- Vomiting both initial and replacement doses at any single time in the treatment (i.e. If the patient vomits both attempts to administer the morning dose that would require withdrawal; however, vomiting the initial morning dose but not the morning replacement dose would not require withdrawal), persistent vomiting
- Severe side-effects necessitating hospitalization
- Progression to severe malaria
- Occurrence during the follow-up of concomitant disease that would interfere with a clear classification of the treatment outcome
- Antimalarial (or antibiotics with antimalarial activity) treatment administered by a third party or self-medication with antimalarial (or antibiotics with antimalarial activity) assessed by asking participants or their caretaker at follow-up visits
- Detection of another malaria species infection during the follow-up
- Erroneous inclusion of a patient outside of the inclusion/exclusion criteria
- Misclassification of a patient due to a laboratory error (parasitemia) leading to the administration of the rescue treatment

**Training for personnel**: Clinicians and laboratory personnel are trained and licensed in Ethiopia. In addition, they will receive approximately 1 week additional training to review the protocol of this study. In addition to technical aspects of specific laboratory techniques and clinical assessments, training will stress the importance of confidentiality, appropriate techniques for obtaining informed consent, Staff will participate in practical exercises. Continued appropriate behavior with regard to informed consent will be reinforced by intermittent observation by the supervisor. The staff will include 1-2 laboratory technicians for microscopy, and 1-2 staff persons for enrollment and clinical assessments.

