**EMERGENCY CARE**

Any patient with treatment failure or recrudescence will receive quinine 10mg/kg/dose every 8 hours for 7 days. This will be given orally unless the patient has persistent vomiting, in which case it will be given IM/IV until the vomiting resolves and then will be switched to oral therapy.

Patients with signs of severe malaria (altered mental status, coma, convulsions, hemoglobin <5g/dl, Respiratory distress, circulatory collapse, or abnormal bleeding), persistent vomiting or severe side effects will be hospitalized and receive parenteral therapy with quinine and relevant supportive treatments, according to National Guidelines.

Any participant who develops urticaria or difficulty breathing following administration of the treatment drug will be treated with diphenhydramine or chlorpheniramine and will be withdrawn from the study. In addition, patient and or their parents, caretakers and family members will be counseled that the patient should not receive additional doses of the antimalarial they were given. These patients will be treated with oral quinine for seven days as per the rescue protocol.

Adult patients and parents with children in the study will be encouraged to return to the clinic for any fever or other signs of illness on any day during the 42 day follow-up period, allowing for early detection and treatment of illness before it becomes severe.

Any hospitalization which occurs during the 42 day follow-up period will be paid for by the study.

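### No rule says which prevails when a parasitemic patient with severe signs meets both a treatment-failure definition and a withdrawal criterion

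*Protocol*

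**What the plan says.** **Signs.** Under Identifying, managing and reporting adverse events: "In the case of any severe adverse reaction (difficulty breathing, convulsions, and change in mental status) subjects will be referred to the district hospital". Under Emergency Care, hospitalization and parenteral treatment are ordered for "Patients with signs of severe malaria (altered mental status, coma, convulsions, hemoglobin <5g/dl, Respiratory distress, circulatory collapse, or abnormal bleeding", and in the same sentence for severe side effects.

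**Failure.** For P. falciparum, early failure includes "Development of danger signs or severe malaria on day 1, day 2 or day 3 in the presence of parasitemia" and late clinical failure includes "Development of danger signs or severe malaria after day 3 in the presence of parasitemia". Neither asks about cause. For P. vivax, the first criterion (repeated in Annex II) is clinical deterioration attributed to P. vivax "illness requiring hospitalization in presence of parasitemia". The second needs parasitemia with a temperature of at least 37.5 °C from day 3. The third needs only parasitemia, from day 7.

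**Withdrawal.** Criteria for withdrawal include "Severe side-effects necessitating hospitalization" and "Progression to severe malaria". Emergency Care adds that a participant with urticaria or difficulty breathing after dosing is treated with "diphenhydramine or chlorpheniramine and will be withdrawn from the study", with no reference to the slide.

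**Analysis.** The data analysis plan excludes withdrawn patients per protocol and, in the survival analysis, keeps them until the last day before drop-out. The End-Points section lists treatment failure and withdrawal as separate valid end-points and does not rank them.

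**The concern.** Failure definitions and withdrawal criteria should either not overlap or be ranked. Here they overlap for the most serious outcomes. If the withdrawal criteria and the analysis rule are applied literally, a parasitemic patient who deteriorates on treatment leaves the failure count. The error runs one way, because such a withdrawal can only lower the reported failure rate. If the outcome definitions are applied literally, the same patient is a failure. Two analysts following the protocol could report different results from the same data.

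The vivax arms have a further weakness. The first vivax criterion depends on a judgement of cause. The protocol's paragraph on bias accepts that treating clinicians know the allocation and intends to rely on objective measures, but this criterion is not one. Days 0 to 2 are the dosing days, when a drug reaction is most likely to be suspected.

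**Working it through.** **Step 1. Set the rules side by side for a patient with a positive slide and convulsions, altered mental status or respiratory distress.**

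| Situation | Failure rule met | Judgement of cause needed? |
|---|---|---|
| Pf, days 1–3 | Early treatment failure | No |
| Pf, after day 3 | Late clinical failure | No |
| Pv, days 1–2 | Criterion 1 only | Yes |
| Pv, days 3–6, afebrile | Criterion 1 only | Yes |
| Pv, days 3–6, temperature ≥37.5 °C | Criterion 2 | No |
| Pv, day 7 onward | Criterion 3 | No |

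In every row a withdrawal criterion can be met at the same time: progression to severe malaria, severe side effects needing hospitalization, or (after a dose) difficulty breathing. No section ranks the two.

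**Step 2. Reproduce the planned precision.** The sample-size section assumes 90% adequate response, 120 patients per arm and 20% loss, and states a 95% exact interval of 82.4% to 95.1%. The Clopper-Pearson interval for 90/100 is 82.4% to 95.1%, so the figure reproduces on 100 evaluable patients. A 20% loss from 120 leaves 120 × 0.8 = 96, where 86/96 gives 81.7% to 94.9%. Both denominators are used below; the difference does not affect this point.

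**Step 3. Effect on the per-protocol estimate.** With f failures among n evaluable patients, handling k of the failures as withdrawals changes the failure proportion from f/n to (f − k)/(n − k). The value of k is not in the protocol. It is an assumption, shown from 0 to 5.

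| n | f | k | Failure estimate (exact 95% CI) |
|---|---|---|---|
| 96 | 5 | 0 | 5/96 = 5.2% (1.7–11.7) |
| 96 | 5 | 1 | 4/95 = 4.2% (1.2–10.4) |
| 96 | 5 | 3 | 2/93 = 2.2% (0.3–7.6) |
| 100 | 10 | 0 | 10/100 = 10.0% (4.9–17.6) |
| 100 | 10 | 1 | 9/99 = 9.1% (4.2–16.6) |
| 100 | 10 | 3 | 7/97 = 7.2% (3.0–14.3) |
| 100 | 10 | 5 | 5/95 = 5.3% (1.7–11.9) |

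For k = 1 the change is (n − f)/[n(n − 1)]. That is 91/(96 × 95) = 1.0 percentage point, or 90/(100 × 99) = 0.9 point.

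For falciparum, the Introduction cites a baseline failure of 0.9% on artemether-lumefantrine, which is 0.009 × 96 = 0.9, about one patient. A single such event would take 1/96 = 1.0% (0.03–5.67) to 0/95 = 0% (0–3.81).

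**Step 4. Effect on the survival estimate.** The patient is followed only to the day before drop-out, so the event is censored. Assuming a Kaplan-Meier estimate (the protocol says only survival analysis), an event on days 1 to 3 with all 120 patients at risk removes a step of at most 1/120 = 0.8 percentage point. The survival analysis therefore does not recover the event.

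**The case against.** A reader might infer that an unblinded clinician's label, drug reaction or severe malaria, by itself decides between failure and exclusion. The protocol does not support that. Progression to severe malaria is itself a withdrawal criterion, so both labels lead to withdrawal, and falciparum failure needs no judgement of cause. For falciparum the defect is only the missing precedence rule.

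A reader might also infer a biased comparison of the two vivax arms. The Limitations section says the study is not powered for differences between arms, and the analysis plan lists only per-arm proportions. What can be affected is each arm's own estimate.

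Further points on the other side have weight:

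- The adverse-event sentence orders referral only. Withdrawal comes from the withdrawal criteria and Emergency Care.
- The sign lists match in substance, not word for word. Difficulty breathing appears in an allergic context, while Annex III describes respiratory distress as acidotic breathing.
- The vivax window is narrow, and the definition is taken from a cited WHO document. But a patient withdrawn in that window receives quinine, so later slides cannot bring the case back under criteria 2 or 3.
- Events should be few. The protocol's one related rate, anaphylactic-type reactions to artemisinins in 1 in 2833, implies 120/2833 = 0.04 per arm of 120. That rate covers allergic reactions only, not severe malaria or convulsions.

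These points limit the size of the problem. They do not supply a precedence rule.

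**Conclusion.** The point holds as a missing order of precedence between the outcome definitions and the withdrawal criteria, with an added dependence on open-label attribution for vivax on days 1 and 2 and in afebrile patients on days 3 to 6. The direction is known: each event handled as a withdrawal makes the drug look better, by about 1 percentage point per protocol and at most about 0.8 point in the survival analysis for an event on days 1 to 3. The per-event sizes rest on 96 to 100 evaluable patients per protocol and 120 at risk early on. The number of events is unknown. One event is small against the planned interval, but with failure reported at 5% or less it is a noticeable share of the failures. It is worth correcting because the correction is cheap and the protocol itself fixes the conflicting rules.

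**What to change.** For outcome classification only:

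1. State in the outcome definitions, the withdrawal criteria and the data analysis plan that a patient who meets a failure definition, within its day window and with a positive slide for the treated species, counts as a treatment failure in both analyses. This applies even if a withdrawal criterion is also met, including progression to severe malaria and the Emergency Care withdrawal for difficulty breathing.
2. Vivax criterion 1 gives no start day. For classification, start it at day 1, so that a reaction shortly after the day 0 dose is not counted as failure. Do not extend the rule to every hospitalization with a positive slide, since that would take in intercurrent illness.
3. Have the attribution in vivax criterion 1 made without knowledge of arm where feasible. Otherwise add a sensitivity analysis that counts every parasitemic hospitalization with severe-malaria signs from day 1 as a failure.
4. Report each such event in the planned safety table as well.

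The cost is a few sentences, plus a masked review of a few cases or one extra analysis. The downside is that a true drug reaction in a parasitemic patient may count as a failure, which is conservative for efficacy. The clinical management wording in the adverse-event, Emergency Care and withdrawal sections should be reconciled separately by the investigators.

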**EMERGENCY CARE**

Any patient with treatment failure or recrudescence will receive quinine 10mg/kg/dose every 8 hours for 7 days. This will be given orally unless the patient has persistent vomiting, in which case it will be given IM/IV until the vomiting resolves and then will be switched to oral therapy.

Patients with signs of severe malaria (altered mental status, coma, convulsions, hemoglobin <5g/dl, Respiratory distress, circulatory collapse, or abnormal bleeding), persistent vomiting or severe side effects will be hospitalized and receive parenteral therapy with quinine and relevant supportive treatments, according to National Guidelines.

Any participant who develops urticaria or difficulty breathing following administration of the treatment drug will be treated with diphenhydramine or chlorpheniramine and will be withdrawn from the study. In addition, patient and or their parents, caretakers and family members will be counseled that the patient should not receive additional doses of the antimalarial they were given. These patients will be treated with oral quinine for seven days as per the rescue protocol.

Adult patients and parents with children in the study will be encouraged to return to the clinic for any fever or other signs of illness on any day during the 42 day follow-up period, allowing for early detection and treatment of illness before it becomes severe.

Any hospitalization which occurs during the 42 day follow-up period will be paid for by the study.

# ETHICAL ISSUES

**Consent Process**

Staff members will fully explain the assessments to the participants and or their caretakers and ask for their consent/assent to participate. The written consent documents in English are attached as Annex VII. These will be translated in Afaan Oromoo and Amharic and then back translated to verify accuracy. These will be read to participants and or their caretakers in their respective local language. If a participant or parent/ guardian are illiterate, the consent form will be read to them in their respective local language and a thumbprint will be accepted as a legally effective signature. Consenting participants and or their caretakers will be advised that they are free to decline any question or procedure and that they may terminate their participation at any time without loss of any benefits.

**Purpose.**  The clinical efficacy of the first-line antimalarials CQ and AL will be assessed using a WHO standardized procedure. These results will be used to assist Ethiopia in re-assessing their national malaria drug policies and investigating therapeutic options for the future.

**Procedures**. During the course of the study, patients will receive an antimalarial and will undergo 9-10 finger pricks to allow monitoring of parasitemia and anemia. Clinical assessments will be made on days 0, 1- 3, 7, 14, 21, 28, 35, and 42.

**Duration of participant involvement.** Patients will be involved in the study from day of enrollment (Day 0) until their 42 day follow-up.

**Experimental products or procedures.** No experimental therapies, products, or procedures will be used in this study. The use of AL for the treatment for Pv is common practice and WHO recommended practice in countries that have adopted AL for first-line treatment of Pf.

**RISKS**

There is minimal physical and psychological risk associated with this study. The patient may experience a brief moment of physical discomfort and/or fear during the blood drawing procedure. There will be blood draws collected by finger pricks.

There is minimal risk associated with taking the treatment drugs. All of the drugs are recommended therapies in Ethiopia, have been widely used, and have been found to be safe. Studies of all of these combinations have reported only mild or moderate adverse events, including dizziness, headache, anorexia, nausea and abdominal pain, noting that these events may also be attributable to malaria.

There are no social risks associated with this protocol. Malaria is a widely recognized disease in Ethiopia, and seeking treatment is socially acceptable. There are no economic risks associated with this study. Patients will be assessed and treated free of charge, and families will be given a stipend of 35 Ethiopian Birr (50 Birr for those accompanied by a parent) per visit to cover their travel expenses. Any hospitalization that results from this study or during the follow-up period will be paid for.

**METHODS TO MINIMIZE RISKS**

In order to minimize risks to patients, subjects will be followed closely for signs of recurrent or recrudescent parasitemia, with clinical exams on days 1- 3, 7, 14, 21, 28, 35, and 42 and malaria smears on all those days except day 1. In addition, patients will be encouraged to return on any other day with signs of illness or fever. All patients will be observed closely for an hour following the first dose of medication; if this is well tolerated, participants will be given the option of taking the evening dose home with them or returning to the clinic in the evening for administration of the drug. Any patient who develops urticaria or difficulty breathing following administration of the treatment drug will be treated with diphenhydramine or chlorpheniramine and will be withdrawn from the study. In addition, participants will be counseled that they should not take additional doses of other antimalarials.

